## Abstract

**Background:**

The literature indicates that current home care service are largely task oriented with limited focus on the involvement of the older people themselves, and studies show that lack of involvement might reduce older people’s quality of life. Person-centred care has been shown to improve the satisfaction with care and quality of life in older people cared for in hospitals and nursing homes, with limited published evidence about the effects and meanings of person-centred interventions in home care services for older people. This study protocol outlines a study aiming to evaluate such effects and meanings of a person-centred and health-promoting intervention in home aged care services.

**Methods/design:**

The study will take the form of a non-randomised controlled trial with a before/after approach. It will include 270 older people >65 years receiving home care services, 270 relatives and 65 staff, as well as a matched control group of equal size. All participants will be recruited from a municipality in northern Sweden. The intervention is based on the theoretical concepts of person-centredness and health-promotion, and builds on the four pedagogical phases of: theory apprehension, experimental learning, operationalization, and clinical supervision. Outcome assessments will focus on: a) health and quality of life (primary outcomes), thriving and satisfaction with care for older people; b) caregiver strain, informal caregiving engagement and relatives’ satisfaction with care: c) job satisfaction and stress of conscience among care staff (secondary outcomes). Evaluation will be conducted by means of self-reported questionnaires and qualitative research interviews.

**Discussion:**

Person-centred home care services have the potential to improve the recurrently reported sub-standard experiences of home care services, and the results can point the way to establishing a more person-centred and health-promoting model for home care services for older people.

**Trial registration:**

NCT02846246.

## Background

This study focuses on older people receiving home care services (HCS) and aims to evaluate the effects and meanings of a person-centred and health-promoting HCS intervention. The intervention is person-centred in that it will focus on the older people’s expressed needs and shared decision making concerning care planning and delivery [1, 2], and it is health-promoting as it aims to enable older people to increase their control over their own health [3]. The intervention will enable the older person and family, together with a contact nurse; to have conversations about and prioritise care content that can satisfy psychosocial, physical, and functional needs of the older person.

In the literature, HCSs nationally and internationally have been criticised for not meeting the psychosocial needs of older people [4, 5]. Older people receiving care in their own homes have reported experiences of being lonely [6], isolated [4, 7], inactive, under-stimulated [4, 5] and experiences of life stress [5]. The essence of this criticism relates to perceptions that HCS are primarily granted and delivered based on physical and functional needs, while psychosocial needs and quality of life needs (QoL) have been given less priority [6]. This means that there seems to be a current gap between needs and services, between expectations and experiences, which may lead to expressions of dissatisfaction.

Satisfaction with HCS has been studied worldwide. For example, Kadowaki et al. [4] showed in a Canadian study that older people receiving HCS, who reported that their psychosocial needs were met, also reported higher levels of satisfaction compared to those with unmet psychosocial needs. Other studies report that older people have limited satisfaction with the HCS they receive [5, 7–12] with respect to: limited help in participating in social and daytime activities [5, 7, 11, 13]; detailed time-saving work schedules resulting in lack of time and stressful visits [8, 9, 11, 12]. Thus there seems to be international consensus indicating that older people experience shortcomings regarding the psychosocial aspects of the care provided by HCS.

In addition, shared decision making and influencing the planning of HCS have been reported as important for older people, for example from studies in Australia and Europe [14–19]. Hautsalo et al. [15], Gill et al. [14] and Kaambwa et al. [17] showed that older people wished for a flexible and adaptable HCS that meets their individual needs. It was described as important to choose and influence daily activities. A trusting relationship between the older person and professional staff is described as essential to enable shared decision making to facilitate the older person’s autonomy and sense of being respected [16, 18, 19]. However, both international [16, 20] and Swedish studies [8, 21, 22] report limited possibilities for older people to make shared decisions about their content of care in HCS. Such findings indicate a need to learn more about the effects and meanings of providing HCS that allows shared decision-making.

Furthermore, it has also been found that quality of care is related to QoL among older people receiving HCS [23]. Low QoL has been found to be associated with reduced ADL function, depression, loneliness, not being engaged in meaningful activities [6, 24, 25], social isolation [24, 26] and pain [6]. However, it has also been shown that high quality care can compensate for the deficiencies mentioned above and result in an improved QoL [23, 27]. It could be hypothesised that when older people with HCS have the opportunity to influence the content of care through shared decision-making, the chances of them having their needs met increase, as does their QoL.

In addition, relatives have an important role in the HCS [28–30] and is often there to assist the older person for example with medications, household duties and personal care [29]. Reports from relatives indicate that they often become more engaged with the older person than what they can manage [30], indicating a strong caregiver burden. In addition, the contact with formal care is often initiated by relatives, who often describe themselves as being the bridge between professional staff and the older person, suggesting that care should be a shared responsibility between the older person, relatives and care staff [30]. Such findings indicate the importance of including the family in interventions, and that implementing shared decision-making might improve relatives’ satisfaction with care as well as reducing caregiver strain.

When it comes to age care staff in home care services, a growing crisis has been described with high turnover rates and challenges in recruiting and retaining skilled care professionals. Staff have reported experiences of dissatisfaction and frustration with work [31–33] with respect to a stressful and hectic work situation [31, 33], increasing demands for efficiency [31], not having sufficient time to converse, provide the “little extras”, and provide care in the psychosocial domain [32]. Not being able to provide care in a way that is perceived as satisfactory has been shown to be a predictor of stress of conscience among care staff [34], and a Swedish study showed that the prevalence of stress of conscience has increased among aged care staff in recent years [35].

A more person-centred approach that builds on shared decision making with care recipients and that systematically explores and documents the person’s subjective experiences, expectations, preferences and needs, and incorporate these in care plans and delivery has been shown facilitating high quality care [36, 37]. There is evidence to suggest that older people in person-centred nursing homes had higher QoL compared to older people in less person-centred nursing homes [38], and older people with mild dementia living at home and receiving PCC and collaborative day-care program described having more meaningful lives and increased wellbeing [27]. Other studies in aged care have shown positive results from implementing a person-centred approach [39–41]. For example, a study that implemented PCC in rehabilitation care resulted in functional improvements and higher satisfaction with care [41]. In addition, Olsson et al. [39] showed that increased involvement in care resulted in lower costs, higher physical function, and shorter stays in hospital after hip fractures. Furthermore, Rokstad et al. [40] showed that PCC of older people with dementia can prevent and reduce agitation and depression. Thus, it seems reasonable to interpret that more person-centred and health-promoting home care services can have the potential to increase shared decision-making, increase the focus on psychosocial issues of care, and increase QoL, thriving and satisfaction with care. Even though few intervention studies exist that have evaluated effects from PCC models on wellbeing and experiences of staff in home care services, the evidence for positive effects such as reduced job stress and strain [42], increased personal and professional satisfaction, [43], and less emotional exhaustion [44] in nursing homes have been reported. The evidence for effects of PCC on relatives’ experiences of home care services is sparse and needs further exploration.

### Rational

The literature review above indicates that current HCS is largely oriented towards physical function and the completion of care tasks, with limited focus on psychosocial needs and on involving older people in care planning and decision making, which leads to dissatisfaction with care and low QoL. The literature also describes home care services as being demanding and challenging to both relatives and staff. This study will explore the extent to which a person-centred and health-promoting intervention focusing on psychosocial needs and shared decision- making can improve QoL and satisfaction with care for older people, as well as improve the experiences of relatives and staff.

### Overall aim

The study in this protocol aims to evaluate the effects and meaning of a person-centred and health-promoting HCS intervention on QoL, thriving and satisfaction with care in older people, on caregiver strain, informal caregiving engagement and satisfaction with care among relatives, and on job satisfaction and stress of conscience among care staff.

### Research questions

To what extent will the intervention have significant effects onQoL, thriving, and satisfaction with HCSs in older people?Caregiver strain, informal caregiving engagement and satisfaction with care among relatives?Job satisfaction and stress of conscience among care staff?
What are the experiences and meanings of the intervention as narrated by older people, relatives and care staff?

## Methods/design

A non-randomized controlled trial with a before/after design will be used to explore the effects of the intervention, and a phenomenological-hermeneutic approach to illuminate meanings of the intervention.

### Participants and setting

All participants will be recruited from one municipality in northern Sweden. Two hundred and seventy older people from one geographical HCS district will be invited to form the intervention group and 270 older people from a different geographical HCS district will be invited to form the control group. Both districts have similar organisations, working conditions, staff skill mix and educational levels. In addition, one relative for each person receiving HCS (*n* = 540) will be asked to participate. Sixty-five HCS staff will be invited to participate in the intervention group and 65 in the control group. The inclusion criteria for the older person will be: 1) aged 65 years or older; 2) living at home and receiving HCS, with at least two visits per month and 3) able to speak Swedish. Inclusion criteria for relatives will be; 1) defined by the older person as his/her relative; 2) able to speak Swedish. Inclusion criteria for staff will be; 1) employed in the HCS district for more than 6 months at baseline, as contact staff and 2) able to speak Swedish. A convenient sub-sample of older people (*n* = 30), relatives (*n* = 30), and HCS staff (*n* = 30) from the intervention group will be invited to participate in qualitative research interviews.

### Power calculations

Sample size calculations for the primary endpoint (NHP) [45], for older people indicate that a sample of *N* = 207 will provide 85% power at the 0.05 significance level to detect case control mean differences of 6, based on previously reported results on the dimension social isolation [46]. Further power calculations indicate that the study is sufficiently powered to detect significant differences for the other National Health Profile (NHP) dimensions and also for the secondary endpoints. To adjust for a drop-out rate of 29% based on study by Rokstad et al. [40], 270 participants will be recruited.

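### Enrolling 270 per arm with 29% drop-out leaves about 192, not the 207 on which the 85% power rests; power is about 82%, and the article is unclear whether 270 are enrolled or invited

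*Protocol article*

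**What the plan says.** Three places in the protocol article bear on this.

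- **Power calculations.** For the Nottingham Health Profile, "a sample of *N* = 207 will provide 85% power at the 0.05 significance level" is claimed "to detect case control mean differences of 6, based on previously reported results on the dimension social isolation". The section continues "To adjust for a drop-out rate of 29" per cent, taken from an earlier study, "270 participants will be recruited". It does not say whether 207 is per arm or in total, and it gives no standard deviation and no number of sides for the test.
- **Abstract, Methods/design.** "It will include 270 older people >65 years receiving home care services", with a matched control group of equal size. Here 270 is a per-group number of people in the study.
- **Participants and setting.** "Two hundred and seventy older people from one geographical HCS district will be invited to form the intervention group", and the same number from a second district for the control group. One relative per older person gives 540 relatives, which confirms 270 per group. The verb here, however, is one of invitation.

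No refusal or uptake rate appears anywhere in the article.

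**The concern.** A drop-out allowance has one job: the number enrolled, less the expected loss, should equal the number the power calculation needs. The article prints all three figures (207, 29% and 270), and they do not meet that condition. The stated power for a primary outcome is therefore not what the design delivers on its own assumptions.

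A second, separate matter is what 270 counts. Refusal before enrolment and drop-out after it are different losses, and the article allows only for the second. If field staff took 270 as the number of invitations, each refusal would deepen the shortfall.

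**Working it through.** **Inputs.** From Power calculations: 207 needed, 85% power, significance level 0.05, drop-out 29%, 270 recruited. From the Abstract and Participants and setting: 270 per group, equal groups. Assumed: a two-sided comparison of two means (one-sided also tried).

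**Step 1. Can 270 be reproduced?**

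- Correct inflation, n/(1 − d): 207/0.71 = 291.5, so 292. This is not 270.
- Multiplying instead, n × (1 + d): 207 × 1.29 = 267.0, so 268 when rounded up. With 30% it is 207 × 1.30 = 269.1, so 270.

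The printed 270 lies close to the multiplied form and 22 below the correct one. The article does not state its method, so multiplication is a likely cause but only an inference. The shortfall does not depend on it.

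**Step 2. What does 270 leave?**

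- 270 × (1 − 0.29) = 191.7, about 192.
- Largest loss that still leaves 207: 1 − 207/270 = 23.3%.

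**Step 3. Power at that number, taking 207 as per arm.** For two means, power is approximately Φ(δ√(n/2)/σ − 1.960). At n = 207 and 85% power, the first term must equal 1.960 + 1.036 = 2.996. It scales with √n, so σ cancels:

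- √(191.7/207) = 0.9623
- 2.996 × 0.9623 = 2.884
- Φ(2.884 − 1.960) = Φ(0.924) = 82.2%

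Using the t distribution with 191 per arm gives 82.1%; a one-sided test gives 82.4%. For reference, a difference of 6 with 207 per arm and 85% power implies a standard deviation of about 20.4, a figure the article does not state.

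**Step 4. Does the result depend on the basis of 207?**

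| 207 is | 270 is | Analysable after 29% loss | Power |
|---|---|---|---|
| per arm | per arm | about 192 per arm | about 82% |
| total | total | about 96 per arm | about 82% |
| total | per arm | about 192 per arm | about 98% |

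The second row is ruled out, because the Abstract and Participants and setting make 270 a per-group number. The third row has no deficit, but then 270 is not 207 inflated for drop-out, which is how Power calculations presents it. The first row is the only one consistent with both the derivation and the per-group use of 270.

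**Step 5. Illustration if 270 were only invited.** At an assumed uptake of 80%: 270 × 0.80 × 0.71 = 153 per arm; √(153/207) = 0.8597; Φ(2.996 × 0.8597 − 1.960) = 73%. Over assumed uptakes of 90% down to 50%, power runs from about 78% to about 53%. These uptake rates are assumptions, not figures from the article.

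**The case against.** The best case for leaving the text alone has three parts.

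*The loss is small.* A move from 85% to about 82% would change no conclusion of the study. This stands, and it limits the weight of the point. It does not make the printed figures agree.

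*The basis of 207 is unstated.* If 207 were the total and 270 enrolled per arm, power would be about 98%. This stands as a caveat: a reader should not infer that the shortfall is the same whichever way 207 is read. It rests on the per-arm reading. That reading is nevertheless the coherent one, since 270 is presented as 207 adjusted for drop-out and 270 is per group everywhere else.

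*The verb of invitation may be loose usage.* Staff are treated the same way: 65 are invited in Participants and setting, yet 65 are included in the Abstract. Power calculations, which sets the sample size, speaks of recruitment. Nothing says that invitation stops at 270. This largely stands. A reader might infer from Participants and setting that the trial is badly underpowered, at 73% or lower; the article does not support that, because it gives neither such a stopping rule nor an uptake rate. What remains is an inconsistency in wording that needs to be settled.

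**Conclusion.** The point holds in limited form. On the article's own figures, 270 enrolled per arm with 29% drop-out leaves about 192 per arm. That gives about 82% power where 85% is stated; 292 per arm would be needed to keep 207. The result assumes that 207 is per arm and that the comparison is a standard one of two means; it does not depend on the standard deviation and hardly on the number of sides. Any further loss from refusals is possible but cannot be sized from the article. Severity is minor to moderate: a sample-size statement that is wrong as printed, with a provable cost of about 3 percentage points.

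**What to change.** 1. In Power calculations, either state that 270 enrolled per arm with 29% drop-out leaves about 192 per arm and about 82% power for the difference of 6, or give 292 enrolled per arm as the number consistent with 85%.
2. State there that 207 is per arm.
3. Use one term for 270 in the Abstract, Participants and setting, and Power calculations, so that it is plainly the number enrolled.

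Restating the power costs only wording and a slightly less favourable figure. Moving to 292 per arm adds 22 older people per arm, 44 in all (584 against 540), and up to 44 relatives. Whether the two districts hold enough eligible people is not stated. The third change is wording only if 270 was always meant as the number enrolled. If it was meant as the number invited, recruitment itself would have to extend until 270 per arm have consented, and the sponsor should say so.

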### Intervention

The intervention is based on the theoretical concepts of person-centredness [1, 2] and health-promotion [3] and builds on four pedagogical phases; theory apprehension, experimental learning, operationalization, and clinical supervision. The content of these phases is further described below. The first intervention phase (10 months) will be followed by a second implementation phase in which the HCS will take over the continuation of the intervention with the research team providing support.

#### Theory apprehension

Firstly, staff will engage in a 90-min web-based educational program on the content, meaning, operationalization and outcomes of the central theoretical components of person-centredness [1, 2], person-centred health and care conversations [47] and the evidence-based and nursing knowledge underpinning these concepts. The purpose is to increase knowledge about these concepts, apply theoretical knowledge to daily work, and gain the skills needed later to complete the person-centred health and care conversations with the older person and their relatives. The web-based part includes video lecturers and self-reflective activities.

#### Experimental learning

Secondly, staff will participate in a seminar (180 min) including supervised skills training, based on Kolb’s experimental learning model [48], in how to explore the needs and wishes of the person receiving care with person-centred health and care conversations. Kolb describes learning as a circular movement between experience and reflection. To develop their skills the staff will engage in role-play interspersed with reflective questions such as: What happened in the conversation? What does it mean? What can I learn from that? How can I use what I have learned?

#### Operationalization

Thirdly, staff will conduct a person-centred health and care conversation (60 min) with each older person participating in the study. The purpose of these conversations is to evaluate the extent to which current HCS practices meet the older person’s needs, to maintain or rearrange the care plan to provide care that maximises older people’s health and satisfies psychosocial as well as physical needs. The conversation will be documented and used to influence changes in the care plans as well as in daily care. In addition, staff will be encouraged to balance the care plans with the daily needs and priorities of the older person, so that the daily work of staff will be increasingly characterised by flexibility in adapting planned activities to the older person’s current needs. The person centeredness will thus influence both the planning and daily provision of care. For example, showering could be replaced by a visit to the library if the older person regards the latter as being significantly more conducive to his/her QoL at the moment.

#### Clinical supervision

Finally, staff will participate in ten group supervisory sessions over the course of seven months. The aim is to support and facilitate ongoing operationalization of the central concepts of person-centred and health-promoting care and to influence practice change for each person receiving HCS by discussing facilitators and barriers to such changes and how to reflect on or resolve these in clinical practice.

### Control group

The control group will be offered one 30-min on-line lecture with state-of-the-art knowledge on contemporary care for people with dementia. A ‘usual care paradigm’ will guide the control units, i.e., a continuation of practice as usual. Control units will receive the intervention protocol and study results at the end of the study.

### Data collection and procedures

Data will be collected by means of self-reported study questionnaires and qualitative research interviews.

